### Secondary Outcomes

Secondary endpoints will comprise the decrease of the Pediatric National Institutes of Health Stroke Scale (PedNIHSS) score from admission to discharge and rate of complications. The study will undergo an interim analysis after the first 50 patients have been enrolled.

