## Introduction

Arterial ischemic stroke (AIS) affects 1.3 to 1.6 per 100,000 children every year in developed countries (1–3), and outcomes are potentially severe, with 70% retaining long-term neurological deficits, 20% suffering recurrent strokes, and 10% of strokes resulting in death of the child (4–6). Risk factors for adult stroke such as atherosclerosis are nearly non-existent in pediatric stroke, so that knowledge and evidence of adult stroke cannot be extrapolated to children. Moreover, a lack of recruitment led to the termination of the prospective randomized TIPS (Thrombolysis in Pediatric Stroke) trial designed to assess the safety of intravenous tissue-type plasminogen activator (iv-tPA) in pediatric patients, highlighting the challenges of randomizing children with acute stroke (7). For mechanical thrombectomy (MT) in adults, several randomized clinical trials published in 2015 have shown the efficacy and safety of endovascular recanalization for large vessel occlusions (LVOs) with large effect size (8). In children, after several case series (9, 10), the retrospective Save ChildS Study recently provided the first systematic evidence for the safety of MT in children (11–13). In this study, the rate of recanalization and adverse events was comparable to large randomized controlled trials in adults, and neurological outcomes of the children were generally favorable. However, definitive conclusions cannot be drawn given the limitations of the Save ChildS Study, which include the lack of a control group of LVO patients not treated by MT and the retrospective design (14). Important questions remain, such as a possible lower age limit to perform thrombectomy in children or the impact of specific etiologies such as cerebral arteriopathies on the safety and efficacy of MT.

With the abovementioned difficulties in recruiting pediatric stroke patients for randomized controlled trials together with the ethical concerns about randomizing children into a non-MT group on the basis of the current knowledge, prospective randomized trials on MT in children are unlikely to succeed. Therefore, a prospective multicenter registry is considered the best option to collect further evidence for performing interventional recanalization in childhood stroke (14, 15).

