### Study Groups

#### Endovascular Group

Patients treated with MT (i.e., groin puncture initiated, including all cases where EVT failed or was interrupted), according to established clinical practice, belong to the endovascular group.

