##### Discharge

Patient logistics (length of stay, transfer destination)PedNIHSSmRSPediatric Stroke Outcome Measure (PSOM)Stroke etiology (according to the childhood arterial ischemic stroke standardized classification and diagnostic evaluation classification)Adverse events (symptomatic ICH, non-symptomatic ICH, hemicraniectomy, external ventricular drainage, other)

##### Day 90 ± 10

mRSPSOMAdverse events (symptomatic ICH, non-symptomatic ICH, hemicraniectomy, external ventricular drainage, pneumonia, recurrent stroke, other)Location (care facility, home)

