#### Study Design

Non-interventional, open-label, prospective, multicenter, observational registry study.

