### Statistical Analyses

Summary tables for patient demographics and baseline characteristics will be provided, and comparisons will be made between study arms for the endovascular and best medical treatment groups. The primary and secondary outcomes will be summarized and compared between study groups for the endovascular and best medical treatment groups.

In general, summaries will be presented by occlusion location within treatment group in the relevant analysis populations. Descriptive statistics for dichotomous/categorical variables will include the number and percent of subjects in each category (including missing), by treatment group. Descriptive statistics for continuous variables will include the number of non-missing and missing variables, minimum, lower quartile, median, upper quartile, maximum, mean, and standard deviation, stratified by treatment group. Regarding comparisons between treatment groups, χ^2^ test (Fisher exact test where appropriate) will be utilized for the comparison of categorical variables, and the *t* test (or the Mann–Whitney *U*-test when appropriate) will be utilized for the comparison of continuous variables. Data for the primary outcome will be presented by treatment group. Confidence intervals for dichotomous or ordinal endpoints will be reported on the odds ratio scale.

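### The raw admission-to-discharge fall in PedNIHSS is compared without adjustment between non-randomised groups, so a difference in admission severity alone can appear as a treatment difference

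*Protocol article*

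**What the plan says.** All references are to the protocol article.

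- **Endpoint.** Secondary Outcomes: "Secondary endpoints will comprise the decrease of the Pediatric National Institutes of Health Stroke Scale (PedNIHSS) score from admission to discharge". The Abstract repeats this. The rate of complications is the only other secondary endpoint named.
- **Comparison.** Statistical Analyses says that the secondary outcomes will be compared between the groups. It names the t test, or the Mann–Whitney U-test when appropriate, which "will be utilized for the comparison of continuous variables". It names no covariate. Occlusion location is used only to lay out summaries.
- **Groups.** Study Design describes a "Non-interventional, open-label, prospective, multicenter, observational registry study". Children treated with thrombectomy "according to established clinical practice, belong to the endovascular group", and the medical group is defined in the same way.
- **Measurement times.** PedNIHSS is listed at admission, at 24 h and at discharge. It is not listed at day 90. Discharge has no fixed day, and length of stay and transfer destination are recorded there.
- **Missing scores.** "Descriptive statistics for continuous variables will include the number of non-missing and missing variables". Nothing is said about a child who dies before discharge.

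**The concern.** A decrease cannot exceed the score a child starts with. If children lose roughly a fixed share of their deficit, the group with the higher admission scores falls by more points, whatever the treatment does. Randomisation would make a baseline gap a matter of chance. Here treatment follows clinical practice, and Patient Population sets no severity threshold and admits occlusions from the terminal carotid and basilar arteries to the M3, A2 and P2 segments. Unequal admission severity is therefore plausible.

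A bias of this kind does not shrink as the registry grows. The false difference stays the same while its standard error falls, so a false positive becomes more likely.

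The time point adds a second problem. If children in one group stay longer, they are scored later in recovery and show a larger fall.

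At stake is one of two named secondary endpoints, in a registry whose Conclusion promises high-level evidence on effectiveness.

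**Working it through.** The article gives no sample size, effect size or standard deviation for this endpoint, so there is no figure to reproduce. The calculations below illustrate the mechanism. Every numerical input is an assumption, except the 50 patients of the planned interim analysis, taken as 25 per group.

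**1. Expected false difference.** Suppose there is no treatment effect and the mean discharge score is slope × admission score in both groups. The mean decrease is then (1 − slope) × mean admission score, and the groups differ by

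false difference = (1 − slope) × baseline gap.

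| Gap at admission | Slope 0.7 | Slope 0.5 |
|---|---|---|
| 2 points | 0.3 × 2 = 0.6 | 0.5 × 2 = 1.0 |
| 4 points | 0.3 × 4 = 1.2 | 0.5 × 4 = 2.0 |
| 6 points | 0.3 × 6 = 1.8 | 0.5 × 6 = 3.0 |

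The result is zero if the gap is 0 or the slope is 1.

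**2. Effect on the planned test.** A simulation with no treatment effect used 1,500 runs per setting. It assumed an admission mean of 9 (plus the gap in one group), admission SD 5, slope 0.5, residual SD 4 and discharge scores floored at 0. The share of runs with p < 0.05 for the unadjusted t test on the decrease was:

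| Per group | Gap 0 | Gap 2 | Gap 4 | Gap 6 |
|---|---|---|---|---|
| 25 | 6% | 13% | 40% | 68% |
| 50 | 4% | 21% | 65% | 94% |
| 100 | 5% | 40% | 92% | >99% |

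The Mann–Whitney test gave nearly the same rates. A linear model for the discharge score with the admission score as covariate gave about 4–6% in every cell. That model is correct by construction here, because admission score is the only difference between the groups.

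**3. Variable time.** Take one recovery curve for both groups, with score at day t = 12 × (0.4 + 0.6 × e^(−t/10)). The decrease is 7.2 × (1 − e^(−t/10)).

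- Discharge at day 7: 7.2 × (1 − 0.497) = 3.6 points.
- Discharge at day 14: 7.2 × (1 − 0.247) = 5.4 points.

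The two falls differ by 1.8 points although the course is identical.

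**The case against.** **An adjusted model may exist elsewhere.** The tests in Statistical Analyses are generic, the article is condensed, and the SAP is not shown. That is fair. But the endpoint, its time point and its test are all written down, and the point concerns what they say, not detail left out. If an adjusted analysis is planned, the published statement should match it.

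**The bias is conditional.** It needs a baseline gap and a slope below 1, and the article reports neither. This stands. The size and direction are unknown, and the point ranges above are illustrations. The design does nothing to secure equal starting scores, however.

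**The timing effect is inferred.** No section says that discharge day depends on recovery or differs between groups. This stands too: a variable time is a fact of the definition, but a bias from it is only plausible. The primary endpoint, mRS at 90 days, supplies a fixed-time comparison.

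**Deaths.** A reader might infer that children who die in hospital are dropped and that this flatters a group. The article does not support that. It neither drops nor scores them, and a rule may stand in the full protocol or SAP. The Introduction's figure, "10% of strokes resulting in death of the child", is a background rate, neither in-hospital nor by treatment group. Equal mortality shifts the between-group difference by zero. A shift needs unequal mortality: if survivors improve by 5 points and each death is assigned −22 (assumed), 5% versus 15% gives (0.95 × 5 − 0.05 × 22) − (0.85 × 5 − 0.15 × 22) = 3.65 − 0.95 = 2.7 points. Deaths can also be counted in the 90-day mRS, so they need not be hidden from the study.

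**Conclusion.** The concern holds for the unadjusted comparison of raw decrease. As written, the comparison carries a false difference of (1 − slope) × baseline gap whenever admission severity differs between the groups and recovery is roughly proportional. With assumed slopes of 0.7 to 0.5 and gaps of 4 to 6 points, that is 1.2 to 3.0 points. With 25 per group and slope 0.5, the t test would be falsely positive in about 40% of cases at a gap of 4 and 68% at a gap of 6.

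Two stronger readings are not supported. The endpoint cannot be said to favour thrombectomy, because the article does not say which group starts worse. Nor can it be said to discard deaths. The variable discharge time is a real weakness of the definition, but its effect on the comparison is unquantified. The point is limited to this secondary endpoint.

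**What to change.** - **Replace the test.** Compare the discharge PedNIHSS between groups by ANCOVA or ordinal regression, adjusting for admission PedNIHSS and other recorded baseline confounders such as age and occlusion site. List the covariates, because the article names none for any model. The raw decrease can stay as a descriptive summary.
- **State how deaths enter.** Rank in-hospital deaths as the worst outcome in that analysis. Ordinal regression takes this directly.
- **Show the timing.** Report length of stay by group beside the result.
- **Use the 24 h score only as a sensitivity analysis.** Clinical and Radiological Assessment times that visit from treatment, not from admission. The Treatment section lists no start time for medically treated children who receive no iv-tPA, so the clock in that group must first be defined. It is therefore not a ready-made fixed-time replacement.

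**Cost.** The admission score, age, occlusion site and length of stay are already collected, so this is a change of wording in the analysis plan. The estimate becomes slightly less simple to describe. Adjustment deals with measured severity only: it does not remove other confounding, and it does not make discharge a fixed time.

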#### Clinical and Radiological Assessment

The following baseline and disease characteristics will be assessed at the timepoint admission, treatment, 24 h after treatment, discharge from hospital, and at day 90 (±10 days).

##### Admission

Patient data (age, year of birth, gender)Patient logistics (symptom onset, admission weekday, date and time of admission, date and time of admission imaging, date and time of last known well, date, and time of symptom onset, referral from other hospital)Pre-existing diseasesMedicationmRS at admission (deficits prior to stroke)PedNIHSSImaging findings (type of admission imaging, occluded vessel, computed tomography or magnetic resonance imaging for Alberta stroke program early computed tomography (ASPECT) score, ASPECT score)

##### Treatment

Treatment with iv-tPA

- date and time of iv-tPA- dose

EVT

- timing (date and time of first angiography image, time of first pass, time of final recanalization result)- type of anesthesia- occluded vessel- stenosis or occlusion in a proximal vessel- number of passes- morphologic appearance (normal, arteriopathy, other)- type of treatment and devices used,- treatment complications [vasospasm, intracerebral hemorrhage (ICH), dissection, other]

##### 24 h

PedNIHSSImaging findings (persistent or new occlusion, type of follow-up imaging, ASPECTS)Adverse events (symptomatic ICH, non-symptomatic ICH, dissection, other)

##### Discharge

Patient logistics (length of stay, transfer destination)PedNIHSSmRSPediatric Stroke Outcome Measure (PSOM)Stroke etiology (according to the childhood arterial ischemic stroke standardized classification and diagnostic evaluation classification)Adverse events (symptomatic ICH, non-symptomatic ICH, hemicraniectomy, external ventricular drainage, other)

##### Day 90 ± 10

mRSPSOMAdverse events (symptomatic ICH, non-symptomatic ICH, hemicraniectomy, external ventricular drainage, pneumonia, recurrent stroke, other)Location (care facility, home)

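### Pneumonia and recurrent stroke are named as adverse events only at day 90, so in-hospital events in children without a day-90 record depend on the unprompted item *other*

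*Protocol article*

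**What the plan says.** The Secondary Outcomes section names two secondary endpoints, the change in PedNIHSS and the "rate of complications". Statistical Analyses says that secondary outcomes are compared between the endovascular and best medical treatment groups.

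Clinical and Radiological Assessment sets the follow-up times as "24 h after treatment, discharge from hospital, and at day 90 (±10 days"), and the sections below it itemise what is recorded at each:

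- Treatment, under EVT: "treatment complications [vasospasm, intracerebral hemorrhage (ICH), dissection, other".
- 24 h: "symptomatic ICH, non-symptomatic ICH, dissection, other". A separate imaging item records whether an occlusion persists or is new.
- Discharge: "symptomatic ICH, non-symptomatic ICH, hemicraniectomy, external ventricular drainage, other".
- Day 90 ± 10: the two hemorrhage items, then "hemicraniectomy, external ventricular drainage, pneumonia, recurrent stroke, other".

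Data come from routine care (Data Collection). Treatment follows clinical practice, not randomisation (Study Groups, Study Design).

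**The concern.** Two of the six events named at day 90, pneumonia and recurrent stroke, are prompted at no earlier visit, yet both can occur during the hospital stay. If a child has no day-90 record, nobody completing that child's forms is ever prompted for these events by name. An event that is not prompted is recorded less reliably than one with its own box, and practice is likely to vary across the 50 centers in nine countries that had agreed to take part by January 2020.

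The complication rate bears on the safety hypothesis of the registry. Incomplete capture would make treatment look safer than it is. Because the groups are not randomised, equal day-90 completeness cannot be taken for granted. If completeness differs, the comparison can shift as well as the level.

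**Working it through.** **Step 1: the lists side by side.**

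| Item | Treatment (EVT) | 24 h | Discharge | Day 90 ± 10 |
|---|---|---|---|---|
| Intracerebral hemorrhage | yes | yes | yes | yes |
| Vasospasm | yes | – | – | – |
| Dissection | yes | yes | – | – |
| Hemicraniectomy, ventricular drainage | – | – | yes | yes |
| Pneumonia | – | – | – | yes |
| Recurrent stroke | – | imaging item only | – | yes |
| *Other* | yes | yes | yes | yes |

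Some differences fit timing: dissection is sought around the procedure, and an early hemicraniectomy can still be ticked at discharge. Pneumonia and recurrent stroke are different, because an in-hospital event has no named place until day 90. A recurrence after the 24 h imaging and before discharge rests on *other* alone.

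**Step 2: what can be computed.** The article gives no complication rate, no death or loss rate before day 90 and no sample size. There is no stated figure to reproduce, and what follows is an illustration on assumed inputs.

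Let *p* be the true risk of the event, equal in both groups (true odds ratio 1); *d* the share of children without a day-90 record; *r* how many times as likely a child with the event is to lack that record; and *q* the share of otherwise missed events caught by *other*. Then

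- share of events without a day-90 record: m = r·d / (p·r + 1 − p)
- recorded rate over all enrolled children: p(1 − m) + p·m·q

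With p = 10% and r = 3, the denominator is 0.3 + 0.9 = 1.2. For d = 10%, m = 0.3/1.2 = 0.25, and the recorded rate at q = 0 is 7.5%. For d = 20%, m = 0.6/1.2 = 0.50, and the recorded rate is 5.0%. The odds ratio is (0.075/0.925)/(0.050/0.950) = 1.54.

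Results over all enrolled children, p = 10%, thrombectomy versus medical:

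| Missing d (MT vs medical) | r | q | Recorded rates | Odds ratio |
|---|---|---|---|---|
| 10% vs 10% | 1 | 0 | 9.0% vs 9.0% | 1.00 |
| 10% vs 10% | 3 | 0 | 7.5% vs 7.5% | 1.00 |
| 10% vs 20% | 1 | 0 | 9.0% vs 8.0% | 1.14 |
| 10% vs 20% | 3 | 0 | 7.5% vs 5.0% | 1.54 |
| 10% vs 20% | 3 | 0.5 | 8.75% vs 7.5% | 1.18 |
| 10% vs 20% | 3 | 1 | 10% vs 10% | 1.00 |
| 20% vs 10% | 1 | 0 | 8.0% vs 9.0% | 0.88 |
| 20% vs 10% | 3 | 0 | 5.0% vs 7.5% | 0.65 |
| 20% vs 10% | 3 | 0.5 | 7.5% vs 8.75% | 0.85 |

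At 10% vs 20% missing, r = 3 and q = 0, the odds ratio is 1.62 for p = 5% and 1.44 for p = 20%.

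If the denominator is limited to children with a day-90 record, the odds ratio is 1.00 at r = 1. At r = 3 (p = 10%) it is 1.36, or 0.73 with the missing shares swapped.

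**Step 3: reading.** Under-recording needs only missing day-90 records and incomplete capture by *other*. With no true difference, a distorted comparison also needs missingness that differs by group. Its direction follows whichever group is less complete.

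**The case against.** The case on the other side is substantial, and most of it stands.

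- A reader might infer that these events are never recorded before day 90. The text does not support that: *other* is open at every visit, and 24 h imaging captures a new occlusion. The weakness is unprompted capture.
- A reader might infer that children who die have no day-90 record. The article does not say so. Data come from routine care, so the form could be completed from the chart, and a 90-day mRS shift analysis makes an entry for a child who died plausible. Nor does the article limit the day-90 list to events after discharge. If that list is cumulative and completed after death, only loss to follow-up remains.
- A reader might take the Introduction's figures, "20% suffering recurrent strokes, and 10% of strokes resulting in death of the child", as 90-day rates. They carry no time window and cannot size this point.
- A reader might infer that the comparison is biased, or even reverses sign. A reversal can be constructed. Assume pneumonia in 10% of survivors and 40% of children who die, with mortality of 5% (MT) and 15% (medical). True rates are 0.95×10 + 0.05×40 = 11.5% and 0.85×10 + 0.15×40 = 14.5%. Recorded rates are 9.5 + 2q and 8.5 + 6q, so the sign reverses at q = 0 (9.5% vs 8.5%). They are equal at q = 0.25, and above that there is no reversal. With only children who have a day-90 record as denominator, the rates are 9.5/0.95 = 10% and 8.5/0.85 = 10%. None of these inputs comes from the document.
- Onset dates, and the risk that one hemorrhage ticked at several visits is counted more than once, are details that an article commonly leaves to the full protocol or SAP. They are not part of this point. Categorical variables are in any case summarised per subject.

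These objections leave one point unanswered: the article itemises its lists, and two events that can occur in hospital are named only at the last visit.

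**Conclusion.** The point holds as a modest ascertainment weakness in one compared secondary endpoint. The complication rate can be understated, and the comparison can move in either direction if day-90 completeness differs between groups. The size cannot be derived from the document. The illustrated odds ratios of 0.65 to 1.54 at p = 10% rest wholly on the assumed risk, missing shares and capture by *other*, and they treat these events alone. The overall complication rate also includes hemorrhage, hemicraniectomy and drainage, which are already prompted at discharge. A definite bias or a reversal of sign is not shown. The primary endpoint is not affected.

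**What to change.** Add pneumonia and recurrent stroke to the adverse-event list completed at discharge or in-hospital death, so that it matches the day-90 list. State that the complication rate counts each child once per event type, from admission to day 90 or death, across all forms.

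The cost is two extra form items, plus completion from the chart for children already entered. Timing-specific items such as vasospasm and dissection can stay where they are.

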#### Data Collection

Data will be collected as part of routine clinical care.

#### Data Ownership

Each participating center remains owner of its data. Upon request, data can be retracted from the database.

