### Patient Population

Patients presenting with AIS from January 1, 2020, will be considered for prospective study enrolment.

The following inclusion criteria apply:

clinical diagnosis of acute ischemic strokeconfirmed diagnosis of arterial occlusion consistent with symptoms, including occlusion of terminal carotid artery, middle cerebral artery (M1, M2, M3 segments), basilar artery, anterior cerebral artery (A1, A2 segments), or posterior cerebral artery (P1, P2 segments)endovascular treatment (EVT) attempted (i.e., groin puncture initiated, including all cases where EVT failed or was interrupted) or best medical treatment including intravenous thrombolysisage <18 years

The following is the exclusion criterion:

perinatal stroke

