#### Best Medical Treatment Group

The best medical treatment group includes patients who are treated with best medical therapy (including systemic thrombolysis), according to established clinical practice.

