#### Publication Policy

Inclusive (multiauthor): those doing the work will receive the credit, every center that contributes a relevant number of cases will have the right of coauthorship in publications.

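### Centres may retract data on request, with no deadline, reason or tie to the analysis set, so cases could leave once treatment and day-90 outcome are known

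*Protocol article*

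**What the plan says.** Data Ownership consists of two sentences: "Each participating center remains owner of its data. Upon request, data can be retracted from the database." The right belongs to the centre and rests on ownership. The section names no last date, no acceptable reason, no unit of retraction (single case or whole centre), no effect on an analysis set and no duty to report what was removed. Nothing else in the article text at hand limits it.

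Three other parts of the article matter here:

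- Study Design describes an open-label observational registry, and Primary Outcomes sets the 90-day modified Rankin score, examined by shift analysis, as the primary endpoint. Statistical Analyses compares it between the endovascular and medical groups and reports intervals as odds ratios.
- Endovascular Group counts a child from the start of the procedure: "groin puncture initiated, including all cases where EVT failed or was interrupted." Best Medical Treatment Group is defined by treatment received: "The best medical treatment group includes patients who are treated with best medical therapy (including systemic thrombolysis), according to established clinical practice."
- Design and the Ethics Statement record that informed consent was waived, with anonymization of the data given as the ground.

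**The concern.** Whether a child's record stays in the database should not depend on how that child did. Under this clause it can. By day 90 the centre knows the treatment and the result, and it may then ask for data to be removed without giving a reason.

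Withdrawal of consent does not account for the clause. Consent was waived because the data are anonymized, and the right is given to the centre as owner, not to the family.

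If removals differ by treatment and outcome together, the group comparison is biased. The loss depends on the outcome itself, so adjusting for age, severity or occlusion site does not repair it. A reader of the final report also could not tell whether it had occurred, because no count of retractions is promised. For a registry that intends to supply high-level evidence on effectiveness and safety, that is a weakness in the definition of the analysed population.

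**Working it through.** The article states no sample size, significance level, outcome rate or retraction rate, so there is no figure of the plan's to reproduce. What follows is an illustration on assumed inputs.

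**Formula.** Split the outcome into good and poor. Let g and b be the fractions of good-outcome and poor-outcome cases that stay in the database, in each group. Then

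observed OR = true OR × (g_MT / b_MT) / (g_med / b_med).

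Three consequences follow:

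- If retraction depends on outcome alone, equally in both groups, the ratio is 1 and the odds ratio is unharmed. The same holds if it depends on treatment alone. The harm needs both.
- If only a fraction r of poor-outcome thrombectomy (MT) cases is lost, the factor is 1/(1 − r), whatever the underlying rate of good outcome.
- If r is the same at every level of a covariate, the same factor applies within every stratum, so adjustment leaves it in place.

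**Illustration, true OR = 1.**

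| Loss r | Poor-outcome MT cases lost: 1/(1 − r) | Poor-outcome medical cases lost: 1 − r |
|---|---|---|
| 10% | 1/0.90 = 1.11 | 0.90 |
| 20% | 1/0.80 = 1.25 | 0.80 |
| 30% | 1/0.70 = 1.43 | 0.70 |

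**Less pure selection.** Assume 50% good outcome in both groups, and that 10% of MT cases are retracted, of whom 20% had a good outcome. The MT group then shows (0.50 − 0.10 × 0.20)/0.90 = 53.3% good outcome, and the OR is (0.533/0.467)/1 = 1.14.

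**Effect on a test.** Assume 60% good outcome in both groups, 20% of poor-outcome MT cases lost, 50 children per group before loss, a two-sided 5% level and the normal approximation for two proportions.

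- MT cases left: 50 × (0.60 + 0.40 × 0.80) = 46, of which 30 are good, so 30/46 = 65.2% against 60%.
- Pooled rate: 60/96 = 0.625. Standard error under the null: √(0.625 × 0.375 × (1/46 + 1/50)) = 0.0989. Standard error otherwise: √(0.652 × 0.348/46 + 0.60 × 0.40/50) = 0.0986.
- Rejection probability: Φ((0.052 − 1.96 × 0.0989)/0.0986) + Φ((−0.052 − 1.96 × 0.0989)/0.0986) = about 8.2%, against a nominal 5%.

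The same calculation gives about 6.5% with 25 per group and 11.5% with 100 per group. Across good-outcome rates of 50% to 80% the ranges are 6.0–6.7%, 7.0–8.4% and 9.2–11.9% for 25, 50 and 100 per group.

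**Limit of the illustration.** The primary analysis is a shift across the whole Rankin scale. The factor above is exact for one cut between good and poor. The effect on a common odds ratio also depends on which grades are lost.

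**The case against.** The best defence is that two short sentences in a condensed article only reserve ownership. Database locks and frozen analysis sets usually sit in a full protocol, analysis plan or site agreement, and none of these is shown. The article does not say that a centre may act at any time or pick single cases. It is also fair that nothing suggests any centre would retract selectively.

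Part of this stands. The text shows that outcome-dependent removal is possible, not that it occurs, and reading the clause as valid at any time goes beyond its words. But this is more than silence on a detail: a right is granted in general terms, and another document would have to narrow it.

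A reader might also infer more from neighbouring sections. The article does not support these readings:

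- **Selective or late entry.** Patient Population says: "Patients presenting with AIS from January 1, 2020, will be considered for prospective study enrolment." That is ordinary wording ahead of eligibility criteria and names prospective enrolment. Rules on consecutive entry and screening logs are what an article leaves to the full protocol. Counting failed and interrupted procedures as endovascular also closes one route by which poor results could be lost. It does not bar retraction, and the medical group has no matching wording.
- **Retraction in response to interim results.** The article says "The study will undergo an interim analysis after the first 50 patients have been enrolled", but not that centres will see the results.
- **Authorship as a motive.** The Publication Policy says that "every center that contributes a relevant number of cases will have the right of coauthorship in publications." If anything, this rewards keeping cases in.
- **Loss of the advance over the earlier retrospective study.** The Introduction names the missing control group as a limitation of that study as well as its design. The concurrent medical group remains either way.

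**Conclusion.** The point holds for the retraction clause alone. As written, it lets data leave the database after treatment and day-90 outcome are known, with nothing to protect the analysis set or to make removals visible. This is worth correcting, but it is not evidence that the comparison is biased.

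The size is unknown. The odds ratios of 1.11 to 1.43, or 0.90 to 0.70 in the other direction, rest on assumed losses of 10% to 30% of poor-outcome cases in one group and none elsewhere, with no true effect. Smaller or less selective losses would do less. The conclusion also assumes that no document outside the article already restricts the clause; if one does, the article should say so.

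**What to change.** Amend Data Ownership as follows:

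1. Accept retraction only before a dated data snapshot set for each analysis, and only for a whole centre or for a documented data-protection reason.
2. Freeze the analysis set at that snapshot, so that later requests do not change that analysis.
3. Report the number, treatment group, timing and reason of all retractions. This needs only a minimal log kept when data are removed.

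The third item is needed even with the first two. A centre could still withdraw as a whole before a snapshot with its outcomes known, and the report is what lets readers see it.

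Centres keep ownership of their data. The cost is an amended paragraph, the matching site instruction, a retraction log and a dated snapshot per analysis. The downside is that some centres may want to negotiate the ownership wording.
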